#### Description of the Non-Immersive VR Exercise Program

Patients will begin with a 5 min warm-up, followed by a 30 min exercise session with VR, with a perceived exertion between 12 and 15 (somewhat hard/hard) on the Borg rating of perceived exertion (RPE). The HD treatment can be carried out simultaneously as the exercises focus on the work of the lower limbs. The muscles that will be mainly exercised are the quadriceps femoris, adductors, abductors, triceps surae, abdominal muscles, and iliac psoas.

The VR used in the study will consist of an adapted version of ACT (*Treasure Hunt*). This is a non-immersive VR system with a playful design that makes it possible to liven up the HD sessions for patients who come for treatment. It consists of a game in which the patient must move their lower limbs, simulating a treasure hunt, where they must hunt some objects and avoid contact with others. The exercise allows the patient to alternate legs when they are tired. The difficulty of the game may be adjusted according to the characteristics of the participants by the means of hardware in a computer or television (usually present in the Haemodialysis Unit) and a Microsoft Kinect^®^ movement tracking system.

The VR session will be defined by the therapists at the beginning of the session through a management tool, where they will schedule rest periods and their duration, as well as the difficulty of the session based on the patient´s performance. Before the start of the first session, the participants will be instructed about the use of the VR system and a test session will be held to confirm that they have understood the execution of the program.

Once the exercise session is over, the patient will perform a gentle stretching session for 5 min. The intradialytic exercise with non-immersive VR to be performed can be seen in Figure 2.

Control group: The participants in this group will exercise with an electric rehabilitation training pedal attached to the bed or HD chair (Figure 3).

The exercise will be performed simultaneously with the non-immersive VR exercise group during the first two hours of HD treatment. As in the other group, three weekly sessions of 30 min will be carried out at an intensity at which the patient perceives an effort between 12 and 15 (somewhat hard/hard) on the RPE scale.

The muscles exercised with this program are the same as those exercised with the VR exercise (quadriceps femoris, triceps surae, adductors, abductors, iliopsoas, and abdominals).

Before the beginning of the exercise, 5 min of warm-up with light stretching will be performed and, at the end of the 30 min, it will be repeated. The static pedal to be used in the study are shown in Figure 3.

Both groups will carry out their exercise programs in the HD room of the hospital, which has separate departments where the patients of one group will not be able to see the exercise performed by the other group.

### 2.4. Functional Assessment of Patients

Functional tests will be carried out on three interspersed days one week before the start of the exercise program, and the tests will coincide with the days that patients received their HD treatment. Patients will be scheduled half an hour before their treatment to perform the corresponding functional tests.

All tests will be repeated when the exercise program is finished at 12 weeks.

#### 2.4.1. First Day of Functional Tests

##### Short Physical Performance Battery (SPPB) Test

Numerous longitudinal epidemiological studies have demonstrated the ability of SPPB to predict dependency, institutionalisation, hospitalisation, and mortality. The scores range from 1 to 12 points and consist of the following tests [41,42]:Three balance tests: Subjects stand with feet together, in semi-tandem, and in tandem, showing whether they can maintain that position for 10 s (Figure 4; score from 0 to 4).

A Walking Test at Normal Speed Over 4 Metres: Two attempts are timed and the shortest of them is recorded. The test is scored from 0 to 4 based on the seconds taken (Figure 5).

STS-5 Test: The test consists of getting up and sitting down five times on a chair without arms placed against the wall. The time taken until the patient is standing after the fifth repetition is measured, and a score from 0 to 4 is assigned. The test must be performed with arms crossed.

The performance of the STS-5 Test can be seen in Figure 6.

One Leg Balance Test: The test is assessed by asking the subjects to raise one leg (the one that gives them the most security), flex it, leaving the other supported, and holding it for as long as possible. The length of time is recorded at the end of the test. The subject can move the arms and flex the knee if necessary to maintain balance. The test ends when the subject uses the arms to support himself or the elevated leg or when 45 s has elapsed. The test is repeated three times and the best time is recorded [44].

The performance of the One Leg Balance Test can be seen in Figure 7.

Timed Up and Go Test: From a standard chair with armrests, the patient must get up, walk 3 metres, and return to the starting position. Time and effort are recorded on the RPE scale [42,45]. (Figure 8).

#### 2.4.2. Second Day of Functional Tests

STS-10 Test [46]: The test measures the number of seconds it takes for the patient to get up and sit down 10 consecutive times in flat shoes. The test is performed on a chair without armrests, approximately 44.5 cm high, 38 cm deep, and leaning against the wall to minimise the risk of falling during the test [47]. The patient must remain seated for a few minutes before carrying out the test, allowing time between this and the previous test. The test must be carried out with the arms crossed over the chest. After the completion of the test, the time needed and the effort perceived with the RPE scale are recorded.STS-60 Test [48]: The patient must perform as many repetitions as possible for 60 s. After that time, the repetitions and the effort perceived on the RPE scale are recorded. The clinically important change for the STS-10 is 8.4 s, and that for the STS-60 is 4 repetitions [49].

The performance of the STS-10 Test and the STS-60 Test can be seen in Figure 9.

#### 2.4.3. Third Day of Functional Tests

##### Six-Minute Walk Test [50,51]

The patient is informed in advance that they should wear comfortable shoes and that the test will be carried out in the corridor of the Haemodialysis Unit of the Alicante Hospital. A heart rate monitor continuously tracks the heart rate. Before performing the test and after resting for five minutes, baseline heart rate and blood pressure are recorded with an electronic blood pressure monitor. Then, the patient covers the pre-established distance as many times as possible in six minutes according to the existing space and markings on the ground (every two metres) and turning without stopping. The instruction that should be given to the patient is ‘walk as far as possible for six minutes’. For those patients who use walking aids in their daily life, they are allowed to carry out the test with them or the assistance of another person, and to stop and restart the march if they need to rest (without stopping the stopwatch). Immediately after the test, the heart rate, blood pressure, and distance travelled are recorded, and the patient is asked to describe the degree of test difficulty on the RPE scale. The clinically important change in this test is equivalent to 66.3 metres [51]. The performance of the Six-Minute Walk Test can be seen in Figure 10.

### 2.5. Plasma Determinations

#### Inflammatory Parameters

The inflammatory markers determined will be IL-6, TNF-α, CRP, ICAM-1, and VCAM-1. All inflammatory markers will be analysed using the enzyme-linked immunosorbent assay (ELISA) technique. The ELISA technique is based on the use of antigens and antibodies labelled with an enzyme, so that the resulting conjugates have both immunological and enzymatic activity. As one of the components (antigen or antibody) is labelled with an enzyme and insolubilized on a support (immunosorbent), the antigen–antibody reaction will be immobilised; therefore, it will be readily revealed by the addition of a specific substrate that, when the enzyme acts, will produce a colour observable by the naked eye or quantifiable by a spectrophotometer or a colorimeter [52].

### 2.6. Psychological Assessment

#### 2.6.1. Multidimensional Questionnaire of Adaptation to the Disease for Renal Patients on Dialysis (CAMAE-RD) [53]

The CAMAE-RD consists of Phase A and Phase B. Phase A, which includes 12 items, collects all of the information from the clinical history of the patient. This phase includes two areas: Data Doctors and Previous Psychopathological History. Phase B, which includes 51 items, is made up of nine areas that form the evaluation of the patient: Sociodemographic Data (six items), Information (nine items), Medication and Diet (three items), Social Support (four items), State of Encouragement (two items), Personal Resources, Coping and Resilience (eight items), Learning and Perceived Changes (five items), Spirituality (two items), and Care Planning (two items). There are four types of questions depending on the type of response: those with a closed character (dichotomous responses, nominal categorical, and 10-point Likert-type scales) and those with an open character (qualitative responses). The increase in the score on the scale with a statistically significant change (*p* < 0.05) between the pre-intervention and post-intervention value will be considered positive.

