Recently, the integration of VR into traditional physical exercise and rehabilitation programs has aroused great interest in the fields of kinesiology and public health. Using VR, it is possible to intensify repetitive tasks and increase visual and auditory feedback, which makes it a novel and attractive therapeutic tool that can be combined with traditional physiotherapy, as it is safe and effective for the patients who use it [32].

Researchers have recently begun to investigate whether the beneficial effects that VR has been shown to have in exercise programs for other populations can be extrapolated to patients with CKF undergoing HD treatment. There are five clinical trials published to date [33,34,35,36,37], the results of which show that the application of VR exercise during HD improves physical function and reduces fatigue and depression in these patients.

In 2019, Segura-Orti and García-Testal conducted a review that reinforced these results, concluding that intradialytic exercise with VR is safe and improves physical function and health-related quality of life in patients on HD. They also concluded that this exercise can be performed safely during the last hours of the HD session [38].

Along the same lines, another review by Olumuyiwa et al. concludes that the use of VR during HD treatment significantly improves the levels of physical activity and fatigue in patients with CKF, as well as increases the levels of adherence and commitment to HD treatment, without the appearance of adverse effects [39].

Currently, only one study has analysed the effect of VR exercise on depression levels in patients on HD, whereas the effect of VR exercise on the inflammatory status of these patients has not been studied at all. It could be expected that the beneficial effects on inflammation are comparable to those obtained with conventional exercise [19], and their psychological state also improves. Therefore, we plan to carry out a study of these characteristics with the aim of determining the effectiveness of an intradialytic exercise program with VR on inflammatory markers, in addition to delving into its effect on functional capacity and psychological state. As a secondary objective, we intend to analyse the levels of adherence to the exercise program and compare the results obtained for all the variables to those of a group that performs intradialytic static pedal exercise.

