### 2.8. Statistical Analysis

The sample size of the study was calculated using the statistical program G-Power (analysis of variance (ANOVA): repeated measures, within/between interaction), assuming a type I error or α of 0.05 (95% confidence interval), a statistical power of 0.80 (type II or β error), and an effect size of 0.25 (mean), requiring the inclusion of 24 patients to ensure the external validity of the study. Considering that there may be losses during the study follow-up, 80 patients will be included: 40 in the control group and 40 in the intervention group.

Intention-to-treat statistical analysis will be performed using the statistical program SPSS 23.0 for Windows (SPSS Inc, Chicago, IL, USA).

The normal distribution of the groups will be verified through the chi-square and Mann–Whitney U tests for correct randomisation.

A mixed two-way ANOVA test will be used to analyse the effect of the VR exercise on functional variables and inflammatory variables in each study group and to analyse the differences between the two groups.

Data will be presented as mean ± standard deviation, setting statistical significance at *p* < 0.05.

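### CAMAE-RD is called positive on a before-after test that leaves out the pedal arm, and the VR-versus-pedal comparison is ranked secondary although the trial is sized on it

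*Protocol article*

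**What the plan says.** Four places in the protocol article bear on this.

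- **Section 2.6.1 (CAMAE-RD).** The criterion is "The increase in the score on the scale with a statistically significant change", with the threshold set at p < 0.05, and such a change "between the pre-intervention and post-intervention value will be considered positive". Neither arm is named.
- **Introduction, last paragraph.** The aim is "determining the effectiveness of an intradialytic exercise program with VR on inflammatory markers", with functional capacity and psychological state added and no comparator named. The next sentence reads "As a secondary objective, we intend to analyse the levels of adherence to the exercise program" and goes on to "compare the results obtained for all the variables to those of a group that performs intradialytic static pedal exercise". The randomised comparison thus sits under the secondary objective, but it covers every variable.
- **Section 2.8 (Statistical Analysis).** The sample size is computed for the within-between interaction of a repeated-measures ANOVA (effect size 0.25, α 0.05, power 0.80, 24 patients required, 80 enrolled as 40 + 40). On the analysis: "A mixed two-way ANOVA test will be used to analyse the effect of the VR exercise on functional variables and inflammatory variables". The sentence applies this both within arms and between them: "in each study group and to analyse the differences between the two groups". The psychological scales are not named there, and no ANOVA term is singled out as the one that decides.
- **Section 3 (Expected Results).** Both arms are expected to improve on inflammatory, functional and psychological measures, with larger effects under VR.

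**The concern.** Randomisation protects one comparison: VR against pedalling. The CAMAE-RD rule does not use it. The control arm also exercises, and the protocol expects it to improve, so a before-after gain in the VR arm contains whatever exercise of either kind does, together with any drift over 12 weeks. A significant gain cannot separate VR from pedalling.

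The parts of the protocol also answer different questions. The sample size is set for a between-arm contrast, the stated main aim has no comparator, and the one outcome with its own significance criterion is judged on change from baseline. Someone following the text literally could report CAMAE-RD as a success for VR on a change that the pedal arm shares, or contrast a significant VR arm with a non-significant pedal arm when the two do not differ.

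**Working it through.** **1. The plan's own figure.** The usual noncentral-F calculation for the interaction uses λ = f²·N·m/(1−ρ), df1 = (k−1)(m−1) and df2 = (N−k)(m−1). Take f = 0.25, k = 2 groups and m = 2 time points (before and at 12 weeks, as section 2.4 states for the functional tests). The correlation ρ is not stated.

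- At ρ = 0.5 the required N is 34. N = 24 gives λ = 0.0625·24·2/0.5 = 6 and power of about 65%.
- At ρ = 0.65 the required N is 26, and at ρ = 0.70 it is 22. A figure of 24 fits a ρ between these, or four time points at ρ = 0.5.

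The stated 24 can therefore be neither confirmed nor refuted, and nothing below depends on it. What matters is that the plan sizes the trial on the between-arm term. With N = 80, ρ = 0.5 and no losses, λ = 0.0625·80·2/0.5 = 20 and power is about 99%, so sample size does not stand in the way of using that term as the criterion.

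**2. Chance that the within-arm rule calls VR positive when the arms do not differ.** Inputs from section 2.8: n = 40 per arm and two-sided α = 0.05. Assumptions: no losses, and the same true change d in both arms, in SDs of the change score. The documents give no value for d, so a range is shown. The paired t test has 39 df and noncentrality d·√40; p is the probability of a significant increase. The arms are independent, so the chance that VR is significant and pedal is not is p(1−p).

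| d | d·√40 | p: VR positive | p(1−p): VR positive, pedal not |
|---|---|---|---|
| 0.2 | 1.26 | 23% | 0.234 × 0.766 = 18% |
| 0.3 | 1.90 | 46% | 0.456 × 0.544 = 25% |
| 0.4 | 2.53 | 69% | 0.694 × 0.306 = 21% |
| 0.5 | 3.16 | 87% | 0.869 × 0.131 = 11% |

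**3. The between-arm test in the same situation.** The true difference is zero, so a two-sided 5% test of the difference in change errs in 5% of trials, half of them (2.5%) in favour of VR. In 20,000 simulated trials at d = 0.3 the rates were 5.1% and 2.5%; the within-arm rule gave 46% VR positive and 25% VR only, matching the table.

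**4. Sensitivity.** At ρ = 0.5 the SD of change equals the SD of the score, because √(2(1−0.5)) = 1. If the common change is instead 0.2, 0.3 or 0.4 SD of the score and ρ = 0.7, the SD of change is √0.6 ≈ 0.77 score SDs. VR is then positive in 36%, 67% or 89% of trials, and VR but not pedal in 23%, 22% or 10%.

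**The case against.** The protocol does not abandon the randomised comparison. Section 2.8 plans a between-group analysis for functional and inflammatory variables and sizes the trial on the interaction. The Abstract proposes comparing VR with pedalling without calling that secondary, section 3 states a comparative hypothesis, and the Introduction's secondary objective extends the comparison to all variables. The CAMAE-RD sentence can also be read as fixing only the favourable direction of change; it does not say that significance in one arm alone demonstrates a VR effect. All of this stands, and it limits the point.

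Some stronger readings are tempting but not supported:

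- **That the trial judges its effects in general on within-arm significance.** The explicit before-after rule covers CAMAE-RD only. None is given for STAI, BDI-II, the functional tests or the inflammatory markers.
- **That the psychological outcomes have no between-arm test.** Section 2.8 does not name them, but the Introduction commits to comparing all variables, and a condensed article may leave the test to a fuller plan.
- **That the relevant error is the chance of exactly one significant arm,** 2p(1−p) = 36%, 50% or 42% for d = 0.2, 0.3 or 0.4. Half of those trials have only the pedal arm significant and cannot yield a false claim for VR.
- **That regression to the mean must inflate the changes.** The eligibility criteria do not select on high depression, anxiety or inflammation scores.
- **That the CAMAE-RD item count supports the point.** The nine listed areas sum to 6+9+3+4+2+8+5+2+2 = 41, not 51, but that is a separate clerical discrepancy.

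What the objection does not remove is that a significance criterion is written for a named outcome without the comparator, and that the comparison the trial is sized on is ranked second. A later analysis plan could correct the first only by contradicting the protocol.

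**Conclusion.** The point holds as an inconsistency of limited scope. The CAMAE-RD criterion ignores the pedal arm, and the ranking of objectives does not match the contrast used for the sample size. With equal improvement of 0.2 to 0.4 SD of change in both arms, the before-after criterion calls VR positive in 23% to 69% of trials, and VR but not pedal in 18% to 25%, against about 2.5% in favour of VR for the between-arm test. These figures rest on assumed changes, 40 analysed patients per arm and no losses, although the protocol expects some. They describe an outcome judged by the before-after rule, which the text sets for CAMAE-RD alone, and are not an error rate for the whole trial. For functional and inflammatory outcomes the weakness is confined to the ranking of the objective and the unstated deciding ANOVA term.

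**What to change.** 1. **Introduction:** state the VR-versus-pedal difference in change from baseline to 12 weeks (group × time) as the main objective and as the basis for any claim that VR is effective.
2. **Section 2.6.1:** replace the before-after criterion with that between-arm contrast, applied to the areas of CAMAE-RD that can be scored. The questionnaire includes nominal and open-ended items, so those areas need listing.
3. **Section 2.8:** name the interaction as the deciding term of the mixed ANOVA, and extend the between-arm analysis to STAI-E, STAI-R, BDI-II and the scorable CAMAE-RD areas.
4. **Throughout:** label within-arm changes as descriptive. Whether p-values are printed beside them is a reporting choice, provided that no claim rests on them.

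The cost is rewording. No extra data or patients are needed. The downside is that a significant change within the VR arm can no longer be reported as a positive result by itself.

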#### 2.6.2. State-Trait Anxiety Inventory (STAI) [54]

STAI is a survey composed of 20 items that assess state anxiety, STAI-E (transient emotional state), and another 20 items that assess trait anxiety, STAI-R (anxious, relatively stable propensity of the participant, in general).

#### 2.6.3. Beck Depression Inventory II (BDI-II) [55]

BDI-II is a tool that assesses the symptoms of depression. The questionnaire consists of 21 questions, providing a range of score between 0 and 63. The questionnaire proposes the following cut-off scores and corresponding degrees of depression: 0–13 indicates minimal depression; 14–19, mild depression; 20–28, moderate depression; and 29–63, severe depression.

### 2.7. Exercise Adherence

Adherence to exercise will be measured by counting the number of exercise sessions in which the patient participates. High adherence will be considered when a patient exceeds 75% of the scheduled sessions (27 of 36 sessions).

### 2.8. Statistical Analysis

The sample size of the study was calculated using the statistical program G-Power (analysis of variance (ANOVA): repeated measures, within/between interaction), assuming a type I error or α of 0.05 (95% confidence interval), a statistical power of 0.80 (type II or β error), and an effect size of 0.25 (mean), requiring the inclusion of 24 patients to ensure the external validity of the study. Considering that there may be losses during the study follow-up, 80 patients will be included: 40 in the control group and 40 in the intervention group.

Intention-to-treat statistical analysis will be performed using the statistical program SPSS 23.0 for Windows (SPSS Inc, Chicago, IL, USA).

The normal distribution of the groups will be verified through the chi-square and Mann–Whitney U tests for correct randomisation.

A mixed two-way ANOVA test will be used to analyse the effect of the VR exercise on functional variables and inflammatory variables in each study group and to analyse the differences between the two groups.

Data will be presented as mean ± standard deviation, setting statistical significance at *p* < 0.05.

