## 3. Expected Results

Both exercise groups (with non-immersive VR and with a static pedal) are expected to see a decrease in their levels of inflammatory markers and improvement in their functional capacity and psychological status. However, higher levels of adherence are expected in the VR group, which will have greater effects on the variables studied in the VR exercise group than in the static-pedal-exercise group.

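### The mixed two-way ANOVA named in section 2.8 is, as written, a complete-case change-score test under an intention-to-treat label; a likelihood-based mixed model would serve better at almost no cost

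*Protocol article*

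**What the plan says.** All the statistical statements are in section 2.8 of the protocol article.

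- **Analysis set:** "Intention-to-treat statistical analysis will be performed using the statistical program SPSS 23.0 for Windows". The term is not defined further.
- **Method:** "A mixed two-way ANOVA test will be used to analyse the effect of the VR exercise on functional variables and inflammatory variables". No test is named for the questionnaires or for adherence.
- **Sample size:** G-Power, "analysis of variance (ANOVA): repeated measures, within/between interaction", with alpha 0.05, power 0.80 and effect size 0.25, giving 24 patients. The number is then raised to 80 (40 per arm). Possible follow-up losses are the only reason given, and no rate is stated.
- **Missing 12-week values:** no imputation or other rule is stated.

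Section 2.4 fixes the time points for the functional tests: one assessment in the week before the program, and then "All tests will be repeated when the exercise program is finished at 12 weeks". Section 2.5 gives no sampling times for the inflammatory markers. I assume the same two.

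**The concern.** A protocol may leave its missing-data method to a later document. This one goes further and fixes a method, and that method, run as named, does not use everyone whom an intention-to-treat analysis is normally taken to include. A patient with a baseline but no 12-week value has no change score and drops out of the group-by-time test.

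Two things are at stake. First, the result would be an effect among patients with both values, reported under a label that suggests more. Second, the change-score contrast does not condition on baseline. If loss depends on baseline and does so differently in the two arms, regression to the mean among the remaining patients produces a spurious difference, and a larger sample does not remove it. Power is the lesser issue.

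**Working it through.** **1. Why the named test is complete-case.** With two time points, the group-by-time F test of a mixed ANOVA is the square of the two-sample t test on (12-week value minus baseline). That difference exists only for patients with both values. By arithmetic, 20% loss leaves 80 × 0.80 = 64 patients and 40% loss leaves 80 × 0.60 = 48.

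**2. The plan's own 24 and its loss allowance.** For the stated G-Power test, the noncentrality is λ = f²·N·m/(1−ρ), with f = 0.25 (read as Cohen's f), two groups, m measurements and correlation ρ. The article states neither m nor ρ.

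| m | ρ | N | λ | Power |
|---|---|---|---|---|
| 4 | 0.5 | 24 | 0.0625×24×4/0.5 = 12.0 | 0.816 |
| 2 | 0.67 | 24 | 0.0625×24×2/0.33 = 9.1 | 0.822 |
| 2 | 0.5 | 24 | 0.0625×24×2/0.5 = 6.0 | 0.649 |
| 2 | 0.5 | 34 | 0.0625×34×2/0.5 = 8.5 | 0.807 |

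So 24 can be reproduced, but only with inputs that the article does not give. The implied allowance is 1 − 24/80 = 70%, or 1 − 34/80 = 57.5% if the base were 34. With m = 2 and ρ = 0.5, 48 completers would still give power 0.92 for f = 0.25.

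**3. Bias if loss depends on baseline.** All inputs here are assumed:

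- no true effect, 40 per arm, unit SD, ρ = 0.5;
- 20% random loss in the VR arm;
- control-arm loss of about 40%, with logit of loss = ln(2/3) − standardised baseline;
- 4,000 simulated trials, with on average 55.3 of 80 patients completing.

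| Estimate of group × time | Bias (SD) |
|---|---|
| Change score, completers (as in the plan) | 0.17 |
| Likelihood estimate keeping all baselines | −0.002 |

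The mechanism is that bias equals (1−ρ) times the amount by which the control completers' mean baseline is shifted. A bias of 0.17 therefore implies a shift of 0.17/0.5 = 0.34 SD. With logit slopes of 0.5, 1 and 1.5 the bias was 0.10, 0.17 and 0.21 SD, and conditioning on baseline left at most 0.002.

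For scale, at ρ = 0.5 the SD of change is √(2×0.5) = 1. With 32 and 23.3 completers the standard error is √(1/32 + 1/23.3) = 0.27, so the bias is 0.17/0.27, about 0.6 of a standard error. The difference detectable if all 80 complete is about 2.80 × √(2/40) = 0.63 SD, and 0.17 is about a quarter of that.

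**4. Precision.** The change-score contrast has variance proportional to 2(1−ρ), and the baseline-conditioned contrast to (1−ρ²). The ratio is (1+ρ)/2, which is 0.75 at ρ = 0.5. This gain holds even with no loss at all.

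**5. What the model does not cure.** Suppose loss is 30% on the pedal and 15% on VR, and lost patients change 0.5 SD less favourably for reasons unrelated to baseline. The bias is then (0.30 − 0.15) × 0.5 = 0.075 SD, or (0.30 − 0.10) × 0.5 = 0.10 SD with 10% loss on VR. In a simulation of the first case with a true contrast of 0.075 SD, the completers' contrast averaged 0.003 and the baseline-adjusted one 0.002. Both miss essentially all of it. Here the bias runs against VR, because the pedal arm loses its poorer responders.

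**The case against.** **The label may be used loosely.** Intention-to-treat can mean only analysis by allocated arm whatever the adherence, and imputation followed by ANOVA would be compatible with both sentences. A full protocol or analysis plan may say so. This stands as far as it goes: the two sentences are not irreconcilable. But the article states neither reading, and under the first one patients without a 12-week value are still left out.

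**A reader might infer that the trial expects large losses.** The text does not support that. It says only that losses may occur. The 70% is a by-product of an unexplained step from 24 to 80.

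**A reader might infer that missing data will differ by arm**, because section 3 says "higher levels of adherence are expected in the VR group". That does not follow. Section 2.7 measures adherence by counting sessions attended. A patient who skips exercise still comes for dialysis, and section 2.4 ties testing to dialysis days and attaches no adherence condition. Unequal loss is possible, for instance if those who stop exercising also decline testing, but it is not predicted.

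**The model is no complete cure.** This also stands. With a single follow-up value, a mixed model with equal baseline means comes close to a baseline-adjusted analysis of completers. It corrects loss that depends on baseline, and not loss that depends on the unseen outcome (step 5).

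**Scope.** The ANOVA is named for functional and inflammatory variables only, so the point cannot be extended to the questionnaires.

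**Conclusion.** The point holds in a limited form. As written, the analysis of the functional and inflammatory variables is a complete-case change-score comparison carrying an intention-to-treat label. The documents do not show that losses will be large or unequal, so no particular bias can be claimed for this trial. If loss differs by arm and depends on baseline, the bias could be of the order of 0.10 to 0.21 SD under the assumptions in step 3. It would be near zero if loss is small or unrelated to baseline. The gain in precision (variance ratio about 0.75 if ρ is 0.5) does not depend on any loss. This is a cheap improvement to a stated method and should be made. It is not a flaw that invalidates the design.

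**What to change.** 1. In section 2.8, replace the mixed two-way ANOVA with a likelihood-based mixed model for repeated measures (SPSS MIXED). It should use every randomised patient with any value, analysed as allocated, with baseline means constrained equal across arms and the 12-week difference as the treatment contrast.
2. In section 2.4, and likewise for the blood samples, state that the 12-week assessments are made in every randomised patient still dialysing in the unit, whatever number of sessions was done. This does most to limit loss that no model can repair.
3. Add two sensitivity analyses: a shift (missing-not-at-random) analysis over a stated range, separately by arm, and a completers' analysis.
4. If the ANOVA is kept without imputation, call it complete-case.

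Cost: a few sentences of analysis wording and slightly more analysis work. The software stays the same. Testing already falls on dialysis days, so no extra visits are needed. The change is best made before outcome data are seen.
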